### Secondary dependent measures

2.4

#### Mediators

2.4.1

All questionnaire-based measurements will be collected electronically using the Research Electronic Data Capture (REDCap [44]) system, a secure, web-based software platform.

**Physical activity enjoyment.** Participants will rate their perceived enjoyment of PA at baseline, 6, and 12-months using the Physical Activity Enjoyment Scale (PACES [45]), an 18-item questionnaire with 7-point bipolar scales where a higher score indicates greater perceived enjoyment. The stem, “Think about the exercise you have been doing…” is followed by items such as, “something I liked–something I disliked”. We will modify the stem to target specific enjoyment for the group to which the participant is assigned. (e.g., “Think about the exercise group you have been participating in during this study…"). The PACES has demonstrated excellent reliability in other adult samples [45].

**Exercise adherence.** Daily attendance logs will be maintained by the exercise leaders supervising each group.

**Self-reported physical activity.** Participants will self-report PA using the long-form of the International Physical Activity Questionnaire (IPAQ; [31]). The 31-item IPAQ was designed to provide an evaluation of PA in four domains: work, household, transportation, and leisure. A reference period of “during the last 7 days” will be used when collecting responses. The eight-day test-retest reliability for PA recall of the IPAQ was good with a median coefficient of *r* = 0.80. Criterion validity using accelerometers was acceptable with a median coefficient of 0.40 [46].

**Adverse events and injuries.** We will assess injuries and other adverse events monthly, using a self-report measure adapted from the one developed by Stathokostas and colleagues [47]. The questionnaire consists of 7-items that focus on the region of the body that is injured as well as the injury severity (i.e., whether the participant should contact or visit his or her PCP). Stathokostas and colleagues reported high test–retest reliability (*r* = 0.76) for this measure, with interrater agreement coefficients (*κ*) greater than 0.80.

**Depression and anxiety.** We will use 11 self-reported questions derived from the National Institutes of Health (NIH)-supported Patient Reported Outcomes Measurement Information System (PROMIS) to assess depression, anxiety, and loneliness. Choi and colleagues reported excellent reliability (*r* = 0.91–0.98) for these measures [48]. Scores from theses subscales are positively correlated with valid other “gold standard” measures [49,50], and are responsive to treatment effects [51]. Participants scoring one or more standard deviations above the mean on the depression and/or anxiety subscales will be contacted by research staff within 48 hours and encouraged to speak with their PCP about their results.

**Loneliness.** The Lubben Social Network Scale (LSNS6) will be used to measure participant loneliness. The LSNS6 consists of 6-items intended to measure the extent of a person's social engagement with both family (3 items) and friends (3 items) [52]. Scores from the LSNS6 exhibit good test-retest reliability (*r* = 0.83) and are associated with future mental health outcomes, such as depression and dementia [53,54].

**Body weight and height.** Body weight and height will be measured using a calibrated scale and stadiometer (Tanita, Inc) [55] during the exercise test visits.

**Blood pressure.** Blood pressure will be assessed during the exercise test visits according to the recommendations of the American Heart Association [56]. Resting blood pressure will be measured with the participant in a seated position using a calibrated aneroid sphygmomanometer.

### Covariates and other variables

2.5

PA **program satisfaction.** Satisfaction for the assigned group (i.e., net promoter score) will be measured at the end of each month using the question: “How likely are you to recommend this program to a friend?” using a 10-point (0 = Not at all likely, 10 = Extremely likely) scale. This single-item question has shown to be predictive of future sales growth in marketing studies [57]. In addition, we developed several face-valid questions to measure anticipatory enjoyment, including 1) “How much, if at all, do you look forward to the exercise sessions?” (0 = Not at all, 4 = Very much), 2) “Have you gotten together, outside of these exercise classes, with someone you met in this program?”, and three open-ended items including 1) "What's the one thing we could do to improve the exercise program?”, 2) "What's the one thing you like best about the exercise program?”, 3) “In one sentence, how would you describe what these exercise sessions are like, if a friend asked you.” A final question will also be posed to the participant to rate the exercise leader who led their most recently attended session, “How would you rate this instructor?” (0 = Poor, 4 = Excellent).

**Exercise self-efficacy.** Exercise self-efficacy will be measured using the 5-item self-efficacy scale developed by Marcus and colleagues [58]. Other studies have reported good internal consistency (Cronbach's *α* = 0.76) and test-retest reliability over a 2-week period (*r =* 0.90) [7].

**Preference for exercising in groups versus alone.** This 4-item measure has been used to assess the preference of adults for exercising alone versus in groups, and in different age groups [59], on a 5-point Likert-type scale ranging from −2 (Very unappealing) to + 2 (Very appealing).

**Competitiveness.** We will assess competitiveness using a 12-item measure developed by Conroy and colleagues [60] that assesses the degree to which subjects endorse varying achievement goals during sport. The Achievement Goal Questionnaire for Sport (AGQ-S) measures four goals: Mastery approach (MAp), Mastery avoidance (MAv), Performance approach (PAp), Performance avoidance (PAv), with 3-items for each construct. Overall, the AGQ-S scores have demonstrated strong psychometric properties with evidence of good 7-day differential stability (and test-retest reliability): MAp 0.77 (0.65), MAv 0.60 (0.55), PAp 0.87 (0.76), PAv 0.80 (0.73), latent mean stability, longitudinal factorial invariance, and external validity [60].

**Sociodemographics and tobacco use.** We will measure age, gender, race and ethnicity, smoking status and education, using standard items [[61], [62], [63]].

## Procedure

3

### Blinding

3.1

The research staff that deliver the intervention will be blinded to the research hypotheses, and those who administer the exercise testing will be blind to both the research hypotheses and the group assignment of each participant.

### Randomization

3.2

Following the baseline exercise visit and accelerometer wear period (see Fig. 1), participants will be radnomly assigned using stratified assignment by age (i.e., those over and under 35 years of age) and biological sex. The randomization will be performed using REDCap software. Following randomization, a research staff member will contact the participants to review their exercise group assignment, where the sessions will be held, what they should bring to each session, and answer any additional questions. Additionally, participants will be given the option to install a smartphone application to receive session confirmations and, if necessary, cancellation notifications from the PA program leaders.

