#### Eligibility criteria

2.2.1

Participants will be healthy, but sedentary, adults between 18 and 50 years of age [29]. The participatns will be considered “sedentary” if they report fewer than 90-minutes of MVPA each week [30], based on questions provided in the International Physical Activity Questionnaire (IPAQ; [31]). Finally, because some participants who are screened will be at increased risk for heart disease (and others may have unrecognized symptoms [32]), a physician must provide clearance for participants who answer affirmatively to any item on the Physical Activity Readiness Questionnaire (PAR-Q; [33]). This clearance is particularly important as the proposed physical activities will be moderate-to vigorous-intensity [34].

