#### Recruitment and screening

2.2.2

We will send recruitment letters to patients in the Penn State Health system who reside within a 10-mile radius of each exercise site. If our recruitment rate is unsatisfactory, we will also use a commercial mailing list provider, such as Lorton Data (Arden Hills, MN). To ensure eligibility and review the study procedures, trained research staff will screen individuals over the phone using a standardized script. Prior to enrollment and any study measures, eligible participants will attend a 60-minute orientation session led by trained research staff in a designated location near each exercise site. Similar orientation sessions have successfully improved retention in weight-loss trials by exposing potential participants to more information about the study and its expectations. The orientation session will include: 1) addressing the time and scheduling demands of enrolling and participating in a 12-month RCT (e.g., considering realizing the difficulty associated with travel to PA program sites/measurement sessions), 2) the barriers to PA change after having been chronically sedentary, overweight, and/or obese (e.g., soreness), and 3) managing expectations for individuals and groups (e.g., not being randomized to the group he or she was hoping to be) [35]. In addition, because commitment devices have been shown to positively influence habit formation [36], at the end of the orientation session, we will ask participants still interested in enrolling to make an informal commitment to attend at least 2 out of 4 exercise sessions per week, by viewing the schedule of available exercise sessions, and personally initialing the days that they intend to participate on a monthly basis. If the individual remains interested after the orientation session, he or she will schedule a baseline visit to sign the informed consent and collect initial measurements.

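### Exercise site is left out of the randomisation strata and the analysis model, although recruitment and group delivery are organised by site; this gives up within-site balance and some precision

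*Protocol article*

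**What the plan says.** All references are to the protocol article.

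- **Strata.** Section 3.2 gives the allocation rule as "stratified assignment by age (i.e., those over and under 35 years of age) and biological sex" and adds that "The randomization will be performed using REDCap software". No other factor is listed.
- **Sites.** Section 2.2.2 sends letters to patients "who reside within a 10-mile radius of each exercise site" and places the orientation session, held before enrolment, "in a designated location near each exercise site". There is therefore more than one site, and a participant's site would normally be known before randomisation. The number of sites is not given.
- **Travel.** The same section lists, among the points to raise at orientation, "considering realizing the difficulty associated with travel to PA program sites/measurement sessions".
- **Delivery.** Both programmes are leader-led group sessions (Sections 3.2.1 and 3.2.2).
- **Role of attendance.** Section 2.1 expects the month-12 fitness difference to arise through better attendance, and Section 4.1.5 treats attendance as a mediator.
- **Analysis.** Section 4.1.1 adds as covariates those variables on which the groups differ significantly at baseline. Section 4.1.3 specifies random regression models. Neither names site.
- **Age range.** Section 2.2.1 admits "healthy, but sedentary, adults between 18 and 50 years of age".

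**The concern.** Site determines who is approached, where sessions take place and, in a group-delivered programme, who exercises with whom. It is also a plausible influence on attendance, because travel is named as a difficulty. The text does not say that site drives attendance; that step is an inference.

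Age and sex strata do nothing to keep the arms even within a site. The baseline-test rule in Section 4.1.1 brings in a site term only if the imbalance happens to reach significance. Smaller imbalances, and the variance that site explains, stay in the comparison. At stake are balance within sites, secured group sizes in both arms at each site, and a modest amount of power.

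Separately, the two age strata are worded as over and under 35, while 35-year-olds are eligible. Read in whole years, the rule does not say where they go.

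**Working it through.** **1. The plan's own figure.** Inputs from Section 4.1: difference 2.5 ml/kg/min, SD 6.0 at each time point, correlation 0.39, two-sided alpha 0.05, power 80%.

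- SD of change = sqrt(6² + 6² − 2 × 0.39 × 6 × 6) = sqrt(43.92) = 6.627.
- Two-sample t-test (noncentral t): power 0.799 at 111 per group and 0.803 at 112. The stated 112 is reproduced.
- 224 × 1.25 = 280, the stated recruitment total.

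The strata do not enter this calculation, so the stated sample size is unaffected by what follows.

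**2. Chance imbalance within a site.** Assumption: four equal sites, 280/4 = 70 people each.

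- Simple 1:1 randomisation: number in PlayFit ~ Binomial(70, 0.5), and 2 × P(X ≤ 30) = 0.282.
- Arms fixed at 140 each overall: hypergeometric, and 2 × P(X ≤ 30) = 0.214.
- A 60:40 split or worse at a given site, arms fixed at 140:

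| Equal sites (assumed) | People per site | Chance of 60:40 or worse |
|---|---|---|
| 2 | 140 | 0.1% |
| 3 | 93 | 2% |
| 4 | 70 | 7% |
| 8 | 35 | 28% |

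**3. Effect of that imbalance on the estimate.** Let site explain a share r of the variance of change, with r = 0.05 to 0.10 (assumption). The site effects then have SD 6.627 × sqrt(r). At one site, the difference between arms in site share has SD (SD of the PlayFit count)/70. Over S sites, the SD of the resulting shift in the treatment difference is sqrt(S) × (SD of count)/70 × 6.627 × sqrt(r).

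- S = 2, r = 0.05: SD of count 4.19, shift SD about 0.12-0.13 ml/kg/min.
- S = 8, r = 0.10: SD of count 2.77, shift SD about 0.23 ml/kg/min.

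The mean shift is zero in every case, and the target difference is 2.5.

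**4. Precision recovered if site is balanced and modelled.** Residual SD = 6.627 × sqrt(1 − r), at 112 per group:

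| r (assumed) | Residual SD | Power |
|---|---|---|
| 0 | 6.627 | 0.803 |
| 0.05 | 6.459 | 0.822 |
| 0.10 | 6.287 | 0.842 |

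**5. Number of cells.** Age by sex gives 4 cells. Two sites give 8 cells of 280/8 = 35 people; four sites give 16 cells of 280/16 = 17.5.

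**6. Age 35.** Ages 18 to 50 span 33 whole years. If ages are spread evenly (assumption), 280/33 = 8.5, so about 8 participants would be 35. A share of 2% to 4% gives about 6 to 11.

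**The case against.** The strongest case against is that the choice of stratification factors is a design preference. Individual randomisation makes site imbalance zero on average, and the significance level already allows for what remains. With two sites and a 10-point gap in site share, explaining away 2.5 ml/kg/min would need the sites to differ in mean change by 2.5/0.10 = 25 ml/kg/min, against an SD of 6.0. More cells with small blocks also make allocation easier to predict when participants know their group. All of this stands, and it limits the point to balance and precision.

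Three stronger readings are tempting, and the text does not support them.

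- **The arms might run at different places, so travel, facility and leader would differ by arm.** Section 3.2 says only that after assignment "a research staff member will contact the participants to review their exercise group assignment, where the sessions will be held". It does not say that location was unknown before or differs by arm, and recruitment and orientation near each site suggest otherwise. An article may leave such logistics to the full protocol.
- **A month-12 difference could not be attributed to the programme.** Chance imbalance does not have that effect in a randomised comparison.
- **Some sites would have too few players for PlayFit.** A 40/30 split still leaves 30 people. Section 3.2.1 also allows uneven teams and has the instructor play.

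On age, someone a month past the 35th birthday is over 35 in ordinary usage, and any allocation table must place 35-year-olds somewhere. This is loose wording, not a rule that cannot be run.

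The baseline-test rule in Section 4.1.1 is not limited to named variables, so it could pick up site. It would do so only when the imbalance is significant, so it does not replace a prespecified term.

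**Conclusion.** The point holds as a matter of efficiency and balance. Site is normally known before randomisation, structures recruitment and group delivery, and is absent from both the stated strata and the stated model. Provided both arms run at every site, the comparison remains unbiased.

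The loss is modest: power of about 0.80 where 0.82-0.84 would be available if site explains 5-10% of the variance of change, and about a 21-28% chance per site of a 40/30 split or worse with four equal sites. The number of sites, their equal size and the variance share are all assumptions, because the article gives none of them. With two sites, serious imbalance is unlikely; with eight, it is common. The stated sample size does not change. The age-35 wording is a minor correction that would not be worth raising alone.

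**What to change.** - **Section 3.2, strata.** Add exercise site, defined as the site of recruitment, as a stratification factor in the REDCap allocation, and state that both arms are offered at each site.
- **Section 4.1.3, model.** Include site, age stratum and sex in the VO2peak model, whatever the baseline tests in Section 4.1.1 show. Stratifying secures the balance; the model term recovers the precision.
- **Section 3.2, wording.** Write the age strata so that 35 falls in one of them, for example 18-34 and 35-50.

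Cost: a new allocation table before enrolment and a few sentences of text. The drawback is more cells, 8 to 16 for two to four sites. Randomly varying block sizes and concealed allocation keep the sequence hard to predict.

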**Fig. 1 fig1:**
[figure not shown]
Study flow-chart.

Participants will be invited to attend up to 4 sessions per week of their assigned group. Similar to the PA programs offered at many health clubs, we will provide different session time options during the week to overcome scheduling barriers. The leaders of both PA programs will be trained to deliver the interventions by the investigators ([name], [name], [name]) and evaluated regularly to ensure fidelity.

#### PlayFit

3.2.1

Each 1-hour PlayFit session will begin with a 5-minute dynamic warmup period of “catch-and-chat”, with all group members, using the sport implement of the day (e.g., soccer ball, Frisbee). Following the warmup, participants will complete up-to 8-minute play periods (i.e., 4mins, 6mins, 8mins per play period during weeks 0–2, 3–5, and 6-weeks to 12-months, respectively, to allow for gradual increase in PA volume) with each play period followed by a 5-minute rest/water break. The warmup and rest breaks are designed to encourage socialization. The exercise leader who oversees the sessions will provide a basic set of rules for each sport during the warmup (see Table 2 for rules for each sport game). The five sport games of PlayFit include soccer and 4 others that each use the rules of ultimate Frisbee (i.e., handball, netball, Ultimate football). Each week, the games played will be rotated, to provide variety. The instructor will also play while supervising to ensure safety and that the core philosophy of PlayFit (i.e., to maximize enjoyment) is maintained. In addition to considering the tenets of self-determination theory, hedonic theory, and interventions among children, some of the additional approaches we use to maximize enjoyment include that the leaders randomly select teams (i.e, no team captains) and switch after each play period, players may rotate in and out for breaks if and whenever they please (i.e., teams do not need to be even at all times), de-emphasizing inter-individual competition (e.g., we do not keep score), positive, generalized encouragement (e.g., no trash-talking, leaders do not criticize performances), and no-contact (i.e., maintain arms-length distance from one another while playing, do not kick at the feet of others). Following the final play period, another 5-minute period of “catch” will allow for a cooldown and more socializing.

**Table 2 tbl2:** General and specific rules and equipment used during PlayFit games.

General Rules		
	• No penalties, players may position themselves anywhere. • Maintain arms-length distance from others when playing • Play begins at midfield/court. • Each period, alternate who starts with possession. • Possession goes to other team after a goal/touchdown. • If ball goes “out of bounds”, an opposing player returns ball to play.	
Game	Equipment	Additional Specific Rules
Soccer	Field markers (cones) Lightweight volleyball, inflated to 2.0 pounds per square inch (PSI). 4′ × 6′ collapsible goal.	• No goaltenders • No digging (kicking) at the feet of others
Ultimate Frisbee™	Field markers (cones) Soft-sided, flexible Frisbee™	• Players may take up to 2-steps before passing to teammate or attempting to score. • Players can hold the ball for up to 3-seconds before needing to pass or attempt to score.
Ultimate football	Field markers (cones) Nerf™ foam football	• Players may take up to 2-steps before passing to teammate or attempting to score. • Players may hold ball for up to 3-seconds before needing to pass or attempt to score.
Handball	Field markers (cones) Voit™ Tuff Coated Handball (6 inches, 5.8 oz) 4′ × 6′ collapsible goal.	• No goaltenders • Players may take up to 2-steps before passing to teammate or attempting to score. • Players may hold ball for up to 3-seconds before needing to pass or attempt to score.
Netball	Field markers (cones) 2 regulation-height basketball hoops. Standard adult-sized basketball inflated to 8.0 PSI	• Players may take up to 2-steps before passing to teammate or attempting to score. • Players may hold ball for up to 3-seconds before needing to pass or attempt to score. • Players may attempt baskets from any location on the playing area.

#### Small Team Training

3.2.2

The STT condition is designed to represent a “standard-of-care” for PA programming, as instructor-led group exercise classes are common at most fitness centers. We have selected a set of movements from common fitness regimens to match the energy expenditure of PlayFit. STT consists of a variety of bodyweight interval exercises. The sessions will consist of: 5 minutes of greetings, small talk, question of the day, 5 minutes of easy movement, 5 minutes of explanation of training session, demonstration of exercises, practice novel or complex moves, followed by 20-30 minutes of training session, and the final five minutes are devoted to stretching and praise. These exercise offered in the sessions will change weekly and will be included in a week-by-week plan for leaders of the Group Exercise condition. In addition, participants will be encouraged to ask questions of the Group Exercise leader at the beginning and/or end of the classes, as this is the standard of care at fitness centers.Because group fitness classes are usually attended by more women than men, we will design the intervention to be attractive to both sexes, by incorporating components of strength training, athletic movements (e.g., high knee runs, block jumps), and martial arts (e.g., kicks, jabs).

## Data analysis

4

### Sample size determination

4.1

Our power and sample size calculations are based on the following considerations. First, studies among untrained adults have shown that supervised group exercise can increase VO_2peak_ by approximately 4 ml/kg/min over 12 months [[64], [65], [66]]. Based on data derived from the National Health and Nutrition Examination Survey (NHANES) among men (*mean*_VO2peak_ = 42.1 ml/kg/minute) and women (*mean*_VO2peak_ = 34.2 ml/kg/minute) 30–39 years of age [67], we assume the baseline VO_2peak_ of participants will be approximately 35.0 (SD = 6.0). The SD of 6.0 is a conservative estimate using data from the Naval Research Lab, where it was 6.3 and 3.9 in men and women, respectively [68]. After 6-months, we anticipate that participants in both PlayFit and STT will improve their VO_2peak_ by approximately 10% (i.e., 3.5 ml/kg/min), owing to similar rates of program adherence. However, after 12-months, we anticipate only those randomized to PlayFit will maintain these changes in cardiorespiratory fitness, due to better program adherence. These differences in adherence will lead to a maintained improvement (versus baseline) in VO_2peak_ of PlayFit participants at 12-months of 3.5 ± 6.0 ml/kg/minute versus 1.0 ± 6.0 for STT. In this case, sample sizes of 112 in each group achieve 80% power to detect a mean difference of 2.5 ml/kg/minute with a standard deviation of 6.0 at the first time point, a standard deviation of 6.0 at the second time point, a two-sided significance level (*α*) of 0.05, and a correlation between measurements of 0.39. To account for participant attrition, we will oversample at a rate of 25%. Therefore, we will recruit up to 280 participants for the proposed study.

